### Studies

#### RT-PCR study

We will target the recruitment of primary care practices involved in the Health Protection Scotland (HPS) Pandemic Influenza Primary Care Reporting (PIPER) sentinel-swabbing scheme, whereby practices are encouraged to obtain nasal/throat swabs from patients of all ages who have symptoms suggestive of influenza. Each general practice is requested to submit five swab samples per week (seven from season 2015/2016) to the West of Scotland Specialist Virology Centre (WoSSVC), Glasgow Royal Infirmary, Glasgow, UK for RT-PCR testing for a range of respiratory pathogens on any patient presenting for consultation in the practice with influenza symptoms across all ages independent of whether the patient has or has not been vaccinated. Data are also collated by HPS on RT-PCR testing patients from swabbing carried out in primary and secondary care for routine diagnostic purposes outside the sentinel scheme. All RT-PCR data on positive and negative tests are held by HPS in the national laboratory database—ECOSS database. WoSSVC is a WHO accredited National Influenza Center, which participates in the quality assurance programme to maintain this status. From 1999, the RT-PCR testing used to confirm respiratory virus type has been found to be highly sensitive for influenza A (H3, H1) and B diagnosis.^37^ Improvements to RT-PCR since 2003 include the development of multiplex testing increasing the number of pathogens tested per PCR assay, however the high sensitivity of these tests remain unchanged.^38^

#### Non-specific clinical outcomes study

To determine the effect of vaccination status on influenza-related primary care consultations, hospital admissions and deaths, secondary analyses will be undertaken using non-specific clinical outcomes derived from primary and secondary care. Influenza-like illness (ILI) and otitis media consultation will be derived from the general practice database. Hospitalisation and cause of death from influenza or pneumonia will be derived from SMR01. We will also include in our secondary analysis a range of asthma-related outcomes, for example, asthma-related consultations/symptoms or measurements, hospitalisations/deaths, rescue medications, etc.

#### Unmeasured confounding and instrumental variable analyses

In addition to Simonsen's Framework, we will also assess the robustness of our results by modelling the effect of an unmeasured confounder on our VE estimates in sensitivity analyses, an approach used previously^39^ and being widely adopted to help explain the role of unknown confounding in observational analyses.^40^ We will vary three factors: the prevalence of the confounder in the vaccinated population, its prevalence in the unvaccinated population and the increased risk of the outcome attributable to the confounder.^41^ The use of influenza vaccine coverage by geographical area has been found to be a strong and valid instrumental variable (IV), which can be used to account for confounding.^42^ Rather than compare patients with respect to whether they received influenza vaccination, this IV behaves like natural randomisation of patients to regional vaccination groups that differ in their likelihood of receiving influenza vaccination. The NSS TRE is an important development in this respect, and we have received permissions to extract granular postcode/geocoding data required to test the validity of this IV analysis in the SIVE II database. We will therefore explore the suitability of vaccination uptake in geographically distinct Health and Social Care Partnership areas or other suitable Health Board areas as a suitable IV. To be valid, this IV needs to be related to exposure status (ie, vaccination status) and not have an independent effect on outcome other than by ways mediated through the exposure.^43^ Furthermore, the IV should not be related to any variables that confound the relationship between exposure and outcome. If an association with confounders is demonstrated, it is assumed that the IV is associated with unmeasured confounders and is therefore not valid. If the IV fulfils these criteria, it can be used in analyses to produce unbiased estimates of VE by accounting for unmeasured confounding.

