## Introduction

Globally, it is estimated that seasonal influenza is responsible for five million cases of severe illness and 500 000 deaths per year, with an estimated cost to the USA of $87 billion per annum.^1^
^2^ Worldwide, there are an estimated 90 million new cases of influenza and 1 million cases of influenza-associated severe acute lower respiratory infection among children.^3^ National influenza vaccination programmes delivered by primary care in the community are important for reducing influenza-related illness, hence the considerable investment in this approach. These programmes previously targeted only older people (65+ years) and people considered at risk with chronic diseases, for example, asthma who are particularly susceptible to becoming seriously ill when they get influenza.

Children are important in the transmission of influenza to the populations at risk of serious complications from influenza and diminished circulation of virus has been predicted to improve herd immunity.^4^ Using evidence generated from epidemiological modelling,^5^ and following advice from the Joint Committee for Vaccination and Immunisation^6^ from September 2013, the seasonal influenza vaccination programme has been extended. In addition to the seasonal trivalent and quadrivalent inactivated influenza vaccine for at-risk individuals and those aged 65+ years, the live attenuated influenza vaccine (LAIV) is offered to all children aged 2–17 years (except those severely immunodeficient or those with severe asthma, prescribed immunosuppressive therapy or oral steroids) by primary care clinicians in general practice and schools in Scotland.

Clinical trials have found benefits of LAIV in healthy children under 7 years of age (most for under 3 years old).^7^

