### Patient characteristics and confounding factors

Key characteristics of patients present in each season of the cohort will be included as confounders in the analyses. Confounders will be defined in each year on the first day of the preinfluenza season (1 September).

*Demographics*: Sex, age band and socioeconomic status will be included in all analyses; socioeconomic status will be measured using quintiles of the Scottish Index of Multiple Deprivation (SIMD). SIMD is an area-based measure of deprivation derived from seven domains including income, employment and education.^31^ Rurality in terms of urban/rural location (one large urban, six remote rural) will also be included in the analysis.

*At-risk groups*: At-risk patients are those with certain comorbidities for whom seasonal influenza vaccination is indicated. Patients will be defined as high risk according to national guidance^29^ if they have one or more of the following conditions:
Asthma;Chronic heart disease;Chronic kidney disease (including renal transplantation) stages 1–2 and 3–5;Chronic liver disease;Chronic neurological diseases;Chronic respiratory diseases;Conditions or drugs causing impaired immune function;Diabetes;Pregnancy (from 2009/2010);Asplenia or dysfunction of the spleen (from 2014/2015);Body mass index (for 2015/2016).

*Chronic diseases*: We will include this for our non-specific clinical outcomes and adverse events. Comorbidity will be defined by the 17 disease categories that constitute the Charlson Comorbidity Index.^32^ This Index has been validated in a number of different databases using codes from healthcare databases.^33^ Furthermore, a study has mapped Read codes from a UK general practice database to the relevant Charlson comorbid disease groups, resulting in a model that performed well in the prediction of 5-year mortality.^34^ These codes will be used to identify comorbidities that are present in a patent's record prior to the start of each preinfluenza season (1 September).

*Smoking status*: This will be derived from primary care data (current smoker, ex-smoker, non-smoker) and determined on 1 September each year.

*Previous vaccinations*: A variable will be included for patients who have received seasonal influenza vaccination in previous seasons to account for the possibility of persisting or reduced VE in the subsequent year.^35^

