### Vaccine effectiveness

#### RT-PCR outcomes

For VE using information from linked virological RT-PCR swab data (a binary event) we will carry out a nested case test-negative control study.^19^ Influenza positivity will be compared with no influenza among patients who have ILI symptoms and tested for influenza. The primary analysis will be through a logistic generalised additive model where the effects of gender, age, socioeconomic status (SIMD^33^) and being in an at-risk morbidity group are adjusted for (a TND study). A spline function for time during each season will be included to model the background rate of influenza and correct for any potential bias associated with the proportions of test-negative and test-positive patients at different periods. VE will be measured by comparing the results from swabs taken after vaccination among those vaccinated to swabs taken among those unvaccinated at the time the swab is collected. Vaccination will be used to define exposure status if it was given at a time point between the 1 September and the end of the influenza season (figure 1). The adjusted estimate of VE=(1**−**OR)×100, where the OR is derived from the coefficient of vaccine status in the model. In our main analysis, we will assess only the first dose when two doses are given. We will carry out analysis stratified by influenza A (H1—including pandemic influenza and H3 subtype where recorded) and B.

We will carry out a number of sensitivity analyses for the primary end point:
*Non-sentinel* versus *sentinel*: We will explore the validity of using laboratory-confirmed influenza tests from non-sentinel primary care and secondary care sources versus sentinel primary care practices. Patient characteristics of individuals swabbed in non-sentinel primary care practices and secondary care will be described and any interaction between source of swab and outcome will be tested.*Negative controls*: As there should be no VE for influenza vaccine for these outcomes, we will explore the use of laboratory-confirmed infections (currently 10 respiratory viruses including rhinovirus and adenovirus) tested using multiplex RT-PCR at the same time as the influenza RT-PCR.*LAIV VE in younger/immunodeficient*: For younger vaccine-naïve or immunodeficient children receiving LAIV, we will account for any second dose in our model.

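### The only stated validity rule for the area-coverage instrument cannot detect herd protection, so an estimate mixing direct and indirect effects could be reported as unbiased individual VE, most clearly for LAIV

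*Protocol article*

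**What the plan says.** The section on unmeasured confounding and instrumental variable analyses credits earlier work with showing area coverage to be a sound instrument and likens it to natural randomisation. The team will "explore the suitability of vaccination uptake in geographically distinct Health and Social Care Partnership areas or other suitable Health Board areas" as an instrument. Three conditions are listed: the instrument is related to vaccination status; it must "not have an independent effect on outcome other than by ways mediated through the exposure"; and it is unrelated to confounders of exposure and outcome.

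Only the last condition comes with a decision rule: "If an association with confounders is demonstrated, it is assumed that the IV is associated with unmeasured confounders and is therefore not valid". The section then concludes: "If the IV fulfils these criteria, it can be used in analyses to produce unbiased estimates of VE by accounting for unmeasured confounding".

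The Introduction, explaining why the programme was extended to children, says that "diminished circulation of virus has been predicted to improve herd immunity". The Abstract gives the same rationale: children are thought to account for much of the transmission to people at risk of complications. The protocol does not connect this rationale with the second IV condition.

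**The concern.** The second condition is the exclusion restriction. The exposure is the individual's own vaccination status, and the instrument is the uptake of the people around that individual. If uptake in an area lowers circulation, it lowers the influenza risk of everyone there, vaccinated or not. That effect does not pass through the individual's own vaccination, so it breaches the restriction.

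The plan names the restriction but gives no means of judging it. An instrument could pass the confounder rule, be declared valid, and yield a figure that adds indirect to direct protection. It would then be read as individual VE freed from unmeasured confounding. Even true randomisation of areas to different coverage would not remove this, so the comparison with natural randomisation gives no reassurance. LAIV effectiveness is part of the study's first objective, and that is where the conflict is sharpest.

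**Working it through.** The protocol states no figure for the IV analysis, so there is none to reproduce. The check sets the passages side by side, then uses the algebra of the ratio (Wald) estimator.

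**1. Can the stated checks see the path?**
- Confounder rule: confounders are defined on 1 September each year (Patient characteristics and confounding factors), before the season's transmission. Their balance across areas says nothing about how coverage later alters circulation.
- Negative controls: the RT-PCR outcomes section plans to use non-influenza respiratory viruses. Herd protection against influenza should leave these unchanged, so a null result there does not clear the instrument.

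**2. General form.** Let c be coverage, VE the direct effect and f(c) the risk in unvaccinated people at coverage c.
- Area risk: r(c) = f(c)(1 − c·VE)
- Wald VE: −r′(c)/f(c) = VE − (1 − c·VE)·f′(c)/f(c)

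The second term vanishes only if area coverage does not change risk in the unvaccinated. It is positive when coverage lowers transmission.

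**3. Two-area illustration.** All inputs are assumed: coverage 50% and 60%, direct VE 40%, unvaccinated risk in the low-coverage area scaled to 1.
- Low-coverage area: 1 − 0.5 × 0.4 = 0.80
- High-coverage area: (1 − d)(1 − 0.6 × 0.4) = 0.76(1 − d), where d is the fall in everyone's risk for 10 points more coverage
- IV VE = [0.80 − 0.76(1 − d)] / 0.10

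| d | High-area risk | IV VE |
|---|---|---|
| 0 | 0.7600 | 40% |
| 1% | 0.7524 | 48% |
| 3% | 0.7372 | 63% |
| 5% | 0.7220 | 78% |

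With no spillover the direct VE is recovered. A small spillover is magnified because it is divided by the assumed coverage gap of 0.10.

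**4. Inputs from the Sample size section.** Children: coverage about 60% (areas at 55% and 65%), direct VE 31%. The 20% positivity cancels. Let s be the assumed proportional fall in risk per unit of coverage, so that s = 0.10 is 1% per 10 points. Then IV VE = 0.31 + s(1 − 0.6 × 0.31) = 0.31 + 0.814s.

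| s | IV VE |
|---|---|
| −0.25 | 11% |
| 0 | 31% |
| 0.10 | 39% |
| 0.25 | 51% |
| 0.50 | 72% |
| 1.00 | 112% (impossible) |

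With a direct VE of zero, the IV VE equals s. The negative row shows that an area-level link in the other direction biases downward.

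**5. Simple epidemic model.** A two-group final-size model with a leaky vaccine was run. Assumptions: R0 1.3 to 1.8, per-exposure VE 31% or 50%, areas 10 points apart. Population shares are from the Sample size section (16% aged 2–17, 18% aged 65+).

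| Target group | Direct VE | IV VE |
|---|---|---|
| Children, equal contact | 20–47% | 23–93% |
| 65+, half contact weight | 25–48% | 27–59% |

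- With children at twice the contact rate, R0 1.3 and per-exposure VE 31%, the IV VE is 87% against a direct 26%. Another scenario exceeds 300%.
- For people aged 65+ at half contact weight the excess is about 2 to 11 points. That small excess depends on the lower contact weight: at equal weight it runs from 4 points (24% v 20%) to 46 points (92% v 46%).

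**The case against.** The strongest reply is that the text is conditional. Herd protection would breach the second criterion, and by the plan's own words no unbiased estimate would then follow. The team promises only to explore suitability. The IV also supplements other work: the same section plans a published framework and a three-factor model of an unmeasured confounder, negative controls are planned for the primary end point, and the strengths and limitations box admits that residual confounding may remain. Neither the primary logistic model nor the Cox models use the IV. No IV estimator is specified, and the primary VE is one minus an odds ratio, so a risk-scale calculation can only illustrate.

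All of that stands, and it limits what may be concluded. A reader might infer that area coverage can never meet the exclusion restriction, that the IV estimate is bound to be inflated, or that the plan relies on the IV alone against unmeasured confounding. The documents support none of these. The breach depends on how far coverage in the instrument group changes transmission. The herd rationale concerns children, whose programme covers three of the 16 seasons, and other area-level links could push the estimate down. A reader might also take the confounder rule for a significance test that trivial imbalance in 1.25 million people would fail. The text names no threshold or unit of analysis, so that is not a finding.

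What the reply does not answer is that a criterion with no means of assessment cannot screen out a bad instrument. The Abstract says an IV analysis will be done to account for confounding and attaches no condition. A condensed article may leave the details of checks to a fuller plan. Here, however, the published text itself draws an inference that its stated rule cannot support.

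**Conclusion.** The point holds in a limited form. By the protocol's own rationale, area coverage can affect a person's influenza risk other than through that person's vaccination. The exclusion restriction is therefore doubtful, most clearly for LAIV in 2013/2014 to 2015/2016. For coverage in people aged 65+ the problem may be slight, if that group contributes little to transmission. Neither the confounder rule nor the negative controls can reveal it. If protective spillover dominates, the IV overstates individual VE.

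The size is unknown. Under the two-area assumptions, a direct VE of 40% becomes 48% to 78% for a spillover of 1% to 5% per 10 points of coverage; across the wider scenarios the excess runs from trivial to absurd. These figures rest on assumed spillover and a risk-scale estimator, and are not predictions for this study. The primary VE estimates are unaffected. What changes is what the IV result may be said to show.

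**What to change.** In the instrumental variable section:

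1. Delete the word unbiased from the concluding sentence.
2. State that, where vaccination reduces transmission, the area-coverage IV estimates a combined direct and indirect (programme) effect.
3. Do not present it as the confounding-corrected individual VE for LAIV.
4. Add a falsification check: does area coverage in the targeted group predict influenza in groups not eligible for that vaccine? An association would count against the exclusion restriction. With few areas, its absence would not prove the restriction holds.

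An analysis restricted to eligible but unvaccinated people should be supportive at most. Being unvaccinated depends on both the instrument and the unmeasured confounders, so selection could produce an association even for a valid instrument.

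The cost is a few sentences and one extra analysis on the linked and geocoded data the study already plans to use. The downside is that the IV may lose its role as a correction for confounding, leaving that to the sensitivity modelling and negative controls already planned.

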#### Adverse events associated with vaccination study

We will explore the use of self-controlled study designs to estimate the risk of adverse events following influenza vaccination.^44^ The assumption underlying these designs is that, in the situation where the adverse event is related to vaccination, the occurrence of an adverse event in the period after vaccination is greater than periods in the same patient that are temporally unrelated to vaccination.^45^ These methods have the advantage of controlling for all fixed individual-level confounders as comparisons are within the same individual rather than between vaccinated and unvaccinated populations. The time period at risk for an adverse event (risk interval) and time period not at risk (control interval) will be determined separately for each outcome.^46^

### Statistical analysis

Baseline characteristics will be summarised by vaccination status for the whole cohort using mean, median or proportion where appropriate together with a measure of dispersion. We will evaluate the baseline characteristics of those tested and not tested using RT-PCR. Missing data will be reported for each variable. A 5% significance level will be used for hypothesis tests for the primary outcome. All p values will be two sided. All analyses will be undertaken in R (V.3.2.3; R Core Team (2015). R: A language and environment for statistical computing. R Foundation for Statistical Computing, Vienna, Austria. URL https://www.R-project.org).

#### Annual and pooled analyses

We will initially analyse each of the 16 influenza seasons separately for the primary outcome. However, a pooled analysis will be performed if increased precision is required (particularly for less common outcomes or where analysing subgroups of patients). We will test the heterogeneity of the vaccine effect over the seasons, by testing for interaction between vaccine status and year for the outcomes. If appropriate, we will then pool the data to give a more powerful analysis than the stratified results. Where heterogeneity occurs, however, the pooled analysis can be restricted or abandoned. In this pooled analysis, we will account for the within-person correlation resulting from repeated measures on the same individual in different influenza seasons.

#### Vaccine uptake

Vaccine uptake will be modelled through logistic regression. ORs (adjusted for age, sex, clinical risk group and deprivation) for differences in proportion of vaccine uptake between different groups of patients (eg, sex, age, SIMD categories and at-risk groups) and for investigating trends in vaccine uptake will be calculated. Vaccine uptake and 95% CIs will be calculated. Practice characteristics will be incorporated by using a multilevel approach.

### Vaccine effectiveness

#### RT-PCR outcomes

For VE using information from linked virological RT-PCR swab data (a binary event) we will carry out a nested case test-negative control study.^19^ Influenza positivity will be compared with no influenza among patients who have ILI symptoms and tested for influenza. The primary analysis will be through a logistic generalised additive model where the effects of gender, age, socioeconomic status (SIMD^33^) and being in an at-risk morbidity group are adjusted for (a TND study). A spline function for time during each season will be included to model the background rate of influenza and correct for any potential bias associated with the proportions of test-negative and test-positive patients at different periods. VE will be measured by comparing the results from swabs taken after vaccination among those vaccinated to swabs taken among those unvaccinated at the time the swab is collected. Vaccination will be used to define exposure status if it was given at a time point between the 1 September and the end of the influenza season (figure 1). The adjusted estimate of VE=(1**−**OR)×100, where the OR is derived from the coefficient of vaccine status in the model. In our main analysis, we will assess only the first dose when two doses are given. We will carry out analysis stratified by influenza A (H1—including pandemic influenza and H3 subtype where recorded) and B.

We will carry out a number of sensitivity analyses for the primary end point:
*Non-sentinel* versus *sentinel*: We will explore the validity of using laboratory-confirmed influenza tests from non-sentinel primary care and secondary care sources versus sentinel primary care practices. Patient characteristics of individuals swabbed in non-sentinel primary care practices and secondary care will be described and any interaction between source of swab and outcome will be tested.*Negative controls*: As there should be no VE for influenza vaccine for these outcomes, we will explore the use of laboratory-confirmed infections (currently 10 respiratory viruses including rhinovirus and adenovirus) tested using multiplex RT-PCR at the same time as the influenza RT-PCR.*LAIV VE in younger/immunodeficient*: For younger vaccine-naïve or immunodeficient children receiving LAIV, we will account for any second dose in our model.

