### Exposure definition

For people in at-risk groups, influenza vaccinations (Trivalent Influenza Vaccine (TIV) and LAIV for preschool children aged ≥2 years) are free and administered by general practice.^29^ Data on influenza vaccination carried out in general practice (including CHI and date of administration) are recorded to enable reimbursement. Information on individuals receiving LAIV in schools is collated in the SIRS database and will be extracted for this analysis.^21^ Vaccination will be used to define exposure status if it is given at a time point between 1 September and the end of the influenza season (figure 1). An individual will be defined as vaccinated 14 days after the seasonal influenza vaccine has been administered.^30^ The time period from the first day of the influenza season to day 14 postvaccination will be defined as ‘unexposed’ and the period from day 14 postvaccination until the end of the influenza season will be defined as ‘exposed’. Therefore, those vaccinated between the start of the preinfluenza period up until 14 days before the influenza season will be defined as ‘exposed’ for the duration of the influenza season. We will exclude participants vaccinated <14 days prior to the RT-PCR test as a sensitivity analysis.

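### The main LAIV analysis keeps swabs taken soon after either vaccine dose and describes no rule for vaccine-strain positives, so live vaccine virus, if the assay detects it, would be scored as influenza

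*Protocol article*

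**What the plan says.** **Outcome.** Under RT-PCR study, "practices are encouraged to obtain nasal/throat swabs from patients of all ages who have symptoms suggestive of influenza". Of the assay, the article says that "the RT-PCR testing used to confirm respiratory virus type has been found to be highly sensitive for influenza A (H3, H1) and B diagnosis". Under RT-PCR outcomes, "Influenza positivity will be compared with no influenza among patients who have ILI symptoms and tested for influenza". Results are stratified by type and subtype. No step is described that identifies a vaccine strain.

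**First dose.** Exposure definition states that "An individual will be defined as vaccinated 14 days after the seasonal influenza vaccine has been administered", and "The time period from the first day of the influenza season to day 14 postvaccination will be defined as" unexposed. It adds: "We will exclude participants vaccinated <14 days prior to the RT-PCR test as a sensitivity analysis". The main analysis therefore retains these swabs, on the unexposed side. RT-PCR outcomes words the contrast differently and does not repeat the lag: "VE will be measured by comparing the results from swabs taken after vaccination among those vaccinated to swabs taken among those unvaccinated".

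**Second dose.** RT-PCR outcomes states: "In our main analysis, we will assess only the first dose when two doses are given". A listed sensitivity analysis takes account of a second dose in the model for younger vaccine-naïve or immunodeficient children. It describes no exclusion window.

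**The concern.** For an inactivated vaccine, the handling of days 0 to 13 is only a question of exposure coding. For LAIV it also bears on the validity of the outcome, because the vaccine is itself an influenza virus. If it can be detected at the swabbed site, a positive test soon after a dose need not mean wild-type infection.

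Such false positives could arise only in recent recipients, so the outcome error would be tied to exposure:

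- After a first dose, under Exposure definition, the swab is a false case among the unexposed. Apparent VE rises.
- After a second dose, the child is normally already exposed, and the swab is a false vaccine failure. Apparent VE falls.
- If the wording under RT-PCR outcomes is followed literally, first-dose swabs count as exposed from day 0, and the direction of the first-dose error reverses.

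The spline for time within season models the background influenza rate, and the negative controls use other viruses. Neither reclassifies a vaccine-virus positive. LAIV effectiveness in children is the first objective, and the ECOSS description mentions 1500 additional tests per season aimed at 2- and 3-year-olds, so the youngest recipients are well represented among the swabs.

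**Working it through.** **Inputs from the article (Sample size):** 1650 child swabs in a season, 60% vaccinated, 20% positivity in the unvaccinated. This gives 990 vaccinated and 660 unvaccinated swabs.

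**The plan's own figure.** The article claims 90% power for a VE of 31%. With 20% v 13.8% (0.20 × 0.69) and a two-sided 5% test:

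- pooled proportion = (132 + 136.62)/1650 = 0.1628
- null SE = 0.01855; alternative SE = 0.01904
- power = Φ[(0.062 − 1.96 × 0.01855)/0.01904] = Φ(1.346) = 91.1%

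The figure reproduces when VE is read as 1 − risk ratio. Read as 1 − OR, power is 79.8%.

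**Misclassification illustration.** These inputs are assumptions that the documents do not give:

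- f: share of the 990 vaccinated swabs falling within 14 days of a dose, 1% to 10%
- s: share of otherwise negative window swabs that are positive from vaccine virus, 10% to 50%
- true VE on the OR scale: 31% or 50%

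The unvaccinated odds are 0.20/0.80 = 0.25. For a true VE of 31% the protected odds are 0.25 × 0.69 = 0.1725, so protected positivity is p = 0.1725/1.1725 = 0.1471.

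*First-dose window coded unexposed* (child not yet protected). Window positivity is 0.20 + 0.80s. Unexposed positivity is [660 × 0.20 + 990f(0.20 + 0.80s)]/(660 + 990f). At f = 5%, s = 30%: (132 + 49.5 × 0.44)/709.5 = 0.2167, odds 0.2767, VE = 1 − 0.1725/0.2767 = 37.7%.

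*Second-dose window coded exposed* (child protected). Exposed positivity is p + f(1 − p)s. At f = 5%, s = 30%: 0.1471 + 0.05 × 0.8529 × 0.30 = 0.1599, odds 0.1904, VE = 1 − 0.1904/0.25 = 23.9%.

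| f, s | True VE 31%: first dose only | True VE 31%: second dose only | True VE 50%: first dose only | True VE 50%: second dose only |
|---|---|---|---|---|
| 1%, 10% | 31.5% | 30.5% | 50.4% | 49.5% |
| 5%, 30% | 37.7% | 23.9% | 54.8% | 43.1% |
| 10%, 50% | 48.8% | 6.3% | 62.9% | 26.3% |

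*Both windows together*, true VE 31%, s = 30%, first-dose f = 5%:

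- second-dose f = 1%: exposed odds 0.1760, VE = 1 − 0.1760/0.2767 = 36.4%
- second-dose f = 5%: VE = 1 − 0.1904/0.2767 = 31.2%, so the two errors nearly cancel

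*First-dose window coded exposed from day 0* (literal wording under RT-PCR outcomes), true VE 31%: 30.3%, 22.8% and 4.7% for the three rows. Not all of this comes from vaccine virus. With s = 0, counting children who are not yet protected as exposed already gives 30.7%, 29.5% and 28.1%.

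**Cost of exclusion.** Removing f of the 990 vaccinated swabs changes power for a VE of 31% (1 − risk ratio) from 91.1% to 91.0% (f = 1%), 90.5% (5%) or 89.9% (10%). On the 1 − OR reading it goes from 79.8% to 79.7%, 79.0% or 78.0%.

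**The case against.** **The premise is outside the documents.** The article credits the assay with high sensitivity by type and subtype. It does not say whether the assay separates strains, and it does not mention detection of vaccine virus after LAIV. This stands. A reader might infer that the RT-PCR cannot tell vaccine virus from wild virus; the documents do not support that. They show only that no separating rule is described.

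**The size is assumed.** Nothing anchors f or s, and at 1% and 10% the effect is negligible. Children vaccinated at least 14 days before the season contribute no first-dose window swabs during it, so f may be low. This stands.

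**The errors offset.** A reader might place every window swab on the exposed side and conclude that VE is heavily understated. Under Exposure definition only second-dose windows belong there, and the article links second doses to a subset of children. The second-dose column at f = 10% is therefore an extreme. This stands too, but equal cancellation is not to be expected when second doses are confined to a subset.

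**Sensitivity analyses exist.** The planned exclusion would reveal a material first-dose effect, and its wording could be stretched to second doses. That is partly right. However, the headline estimate stays uncorrected, and reach to second doses is unclear when the main analysis disregards them.

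**It is a condensed article, and LAIV covers three of 16 seasons.** Laboratory handling of vaccine-like strains may well sit in a fuller document, and its absence alone would be no finding. The article does, however, state which rule is main and which is sensitivity, and that choice is what is questioned.

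**The 14-day window was set for another purpose.** It marks when a person counts as vaccinated. Nothing ties it to how long vaccine virus is detectable. This stands as a limit on the remedy.

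**Conclusion.** The point holds conditionally. As written, the main LAIV analysis retains swabs taken soon after either dose, treats any influenza-positive test as a case, and gives no rule for vaccine-strain positives. Exposure definition and RT-PCR outcomes also differ on which side first-dose window swabs fall.

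Whether this biases VE depends on the assay detecting vaccine virus, which the documents neither state nor rule out. If it does, the error is differential: upward through first-dose windows under the 14-day rule, downward through second-dose windows. For a true VE of 31%, the single-window results run from a shift of about half a point at the low end to 48.8% or 6.3% at the extremes, all on assumed inputs. The errors partly offset, so neither the size nor the sign of the net bias can be fixed from the article, and it may be small.

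This is not a demonstrated failure of the endpoint. It is an avoidable exposure to differential outcome error in the first objective, and it should be changed because the remedy is cheap.

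**What to change.** 1. In the main LAIV RT-PCR analysis, exclude from both cases and controls any swab taken less than 14 days after any LAIV dose, first or second.
2. Keep the analysis that includes those swabs as the sensitivity analysis, reversing the present order for LAIV.
3. Do not count as a case any positive that the laboratory record already identifies as vaccine strain. State whether the record can show this, and ask the laboratory whether 14 days is an adequate window for vaccine-virus detection.
4. Reconcile Exposure definition with RT-PCR outcomes so that both give the same status to a swab on days 0 to 13, and state how the days after a second dose are treated.

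The rule uses vaccination and swab dates that are already linked. It loses perhaps a few percent of child swabs. Even at 10% of vaccinated swabs, power falls by about one point on the basis that reproduces the plan's figure (91.1% to 89.9%), and by just under two on the OR scale (79.8% to 78.0%).
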